## Methods

### Overview of the study design

This single-blinded, 24-week, parallel-group randomized controlled trial with a 1:1 allocation ratio will be conducted in Changsha, China. Patients with T1DM will be randomly allocated into one of two groups: automated, individualized education through an app, and artificial intelligence or routine care. The intervention will last for 24 weeks. The primary outcome will be the change in HbA1c from baseline to week 24 (see flowchart in Fig. 1).

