### Sample size estimation

We propose to enroll 138 T1DM patients including withdrawals, 69 in the smartphone app group and 69 in the routine care group. The sample size estimation is based on the hypothesized changes in the primary outcome HbA1c. Details are presented below.

The primary analysis will compare the level of HbA1c between the smartphone app group and the routine care group. In a recent meta-analysis [11], data from seven RCTs that compared the difference in HbA1c between smartphone app and usual care groups were extracted, and the pooled mean difference was − 0.6%, which was used as the expected effect of this RCT. Using a two-sided hypothesis test at a 5% significance level, with an allocation ratio of 1:1, a total of 110 T1DM patients will be needed to detect a difference in HbA1c between the smartphone app group and routine care group of 0.6% with 80% power. The withdrawal rate among the RCTs included in the meta-analysis ranged from 0.0 to 26.4%, with a median of 8.4% [11]. We conservatively used a drop-out rate of 20%, yielding a total sample size of 138 (69 in the smartphone app group and 69 in the routine care group).

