#### Data analysis

The primary data analysis will be conducted by using data collected at week 24 under the intention-to-treat principle by including all the randomized patients in the data analysis. Missing data will be filled in with a multiple imputation method under the “missing at random” assumption [35]. Any substantial difference in baseline characteristics will be adjusted with mixed-model regression analysis. Between-group differences will be assessed for the smartphone app group versus the routine care group. Relative risk reductions with 95% CIs will be calculated for dichotomous outcomes. The mean difference with standard deviation (SD) will be used to measure the treatment effect for continuous outcomes.

Secondary data analysis will use data collected at week 12 and week 24. All analyses will follow the same template as the primary data analysis by using a mixed model to adjust for imbalanced baseline characteristics. Linear regression will be used for continuous outcomes, and logistic regression will be used for binary outcomes. Model assumptions will be checked by regression diagnostics for all regression models. Predefined moderators including psychological and psychosocial mediators (e.g., depression, anxiety, self-efficacy) will be examined for treatment interactions. The Bonferroni method will be adopted to adjust the significance level under the circumstance of multiple testing. Furthermore, longitudinal analysis in which data collected at baseline, week 12, and week 24 will be jointly analyzed with appropriate mixed models. The time point will be included as a categorical fixed factor with the first-order autocorrelation of the errors and random intercepts. Monthly data collected on HbA1c during the intervention period will be analyzed with similar mixed models.

A sensitivity analysis will be conducted by using per-protocol data and excluding those patients who drop out of the RCT. The results from the sensitivity analysis might provide some pragmatic evidence from the real world regarding the effectiveness of the smartphone app for controlling T1DM. All statistical tests will be two-sided, with *p* < 0.05 considered to indicate statistical significance.

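### The secondary three-visit HbA1c model names a covariance that, as usually fitted, gives all visits one variance, although the entry rule probably narrows baseline; a week-24 contrast from it would likely have an SE about 1–10% too small

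*Protocol article*

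**What the plan says.** The Data analysis section sets the main comparison first: "The primary data analysis will be conducted by using data collected at week 24 under the intention-to-treat principle". The overview of the design defines the outcome: "The primary outcome will be the change in HbA1c from baseline to week 24".

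Under the secondary analysis the article adds a "longitudinal analysis in which data collected at baseline, week 12, and week 24 will be jointly analyzed with appropriate mixed models", and then fixes the structure: "The time point will be included as a categorical fixed factor with the first-order autocorrelation of the errors and random intercepts". It does not say which contrast this model will report (the arm difference at week 24 or the difference in change), and it names no alternative covariance. The same paragraph promises that "Model assumptions will be checked by regression diagnostics for all regression models". A further sentence applies similar models to a monthly HbA1c series.

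Table 2, inclusion criterion 5, requires HbA1c above 7.0%, with no upper limit.

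**The concern.** A random intercept plus first-order autoregressive errors with a single residual variance has three parameters over three equally spaced visits. It makes the variance identical at baseline, week 12 and week 24, and makes the baseline–week-12 covariance equal to the week-12–week-24 covariance.

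Baseline HbA1c is one of the modelled outcomes, and the entry rule cuts its distribution from below. Follow-up values are not cut directly; they lose variance only through their correlation with baseline. If the variances were equal before selection, they are no longer equal after it. The single variance that the model fits then lies between the smaller baseline value and the larger week-24 value, so a week-24 comparison that uses it looks more precise than it is. At stake are the intervals and p-values of the only described analysis that uses all three HbA1c visits jointly.

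**Working it through.** **The plan's own figures.** The article gives no standard error, variance or correlation for this model, so there is no stated figure to reproduce for it. The sample size does reproduce in part. The inflation is 110 / (1 − 0.20) = 137.5, rounded up to 138. For "detect a difference in HbA1c between the smartphone app group and routine care group of 0.6% with 80% power" at two-sided 5%, 55 per arm implies SD = 0.6 / (2.80 × √(2/55)) = 1.12. That SD is solved backwards from 110 and is not stated, so I use it only as the low end of the range.

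**Assumptions (none in the documents).** HbA1c is normal before selection, with the same mean and SD at each visit. Mean 7.5–9.5, SD 1.12–2.0, correlation over 12 weeks 0.60–0.80 and over 24 weeks 0.50–0.70. The baseline sample is the one used for eligibility. Data are complete.

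**Step 1, effect of the cut at 7.0.** Let a = (7.0 − mean)/SD, λ = φ(a)/(1 − Φ(a)) and d = λ(λ − a). After selection, Var(baseline) = SD²(1 − d) and Var(visit t) = SD²(1 − r²d), where r is the correlation of visit t with baseline.

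Example: mean 8.0, SD 1.5, r = 0.75 and 0.65. Then a = −0.667, λ = 0.427, d = 0.468.
- Baseline: 2.25 × 0.532 = 1.198, SD 1.09
- Week 12: 2.25 × (1 − 0.5625 × 0.468) = 1.658, SD 1.29
- Week 24: 2.25 × (1 − 0.4225 × 0.468) = 1.806, SD 1.34

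**Step 2, fit the named structure.** The maximum-likelihood fit of random intercept plus AR(1) to this covariance gives a common SD of 1.24. Model SE over true SE for the week-24 arm difference is 1.242/1.344 = 0.925. With 55 per arm, the model reports √(2/55) × 1.242 = 0.237 where the true value is 0.256.

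**Step 3, type I error.** It is 2[1 − Φ(1.96 × ratio)] = 2[1 − Φ(1.81)] = 7.0%. Constraining the two arms to a common baseline mean leaves it at 7.0%. For the difference in change from baseline the ratio is 1.016 and the type I error 4.6%.

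**Step 4, range.** The week-12 to week-24 correlation is set equal to the 12-week value.

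| Mean, SD, r (12 wk / 24 wk) | SD after selection (0, 12, 24) | Week-24: ratio, type I error | Change: ratio, type I error |
|---|---|---|---|
| 7.5, 2.0, 0.60/0.50 | 1.30, 1.78, 1.85 | 0.895, 8.0% | 1.035, 4.3% |
| 8.0, 1.5, 0.75/0.65 | 1.09, 1.29, 1.34 | 0.925, 7.0% | 1.016, 4.6% |
| 8.5, 1.5, 0.80/0.70 | 1.19, 1.31, 1.36 | 0.947, 6.4% | 1.009, 4.8% |
| 9.0, 1.5, 0.75/0.65 | 1.28, 1.38, 1.41 | 0.961, 6.0% | 1.008, 4.8% |
| 9.5, 1.12, 0.80/0.70 | 1.08, 1.09, 1.10 | 0.991, 5.2% | 1.001, 5.0% |

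Over all 45 combinations of five means, three SDs and three correlation patterns, the week-24 ratio was 0.895–0.991 (type I error 5.2–8.0%). The change contrast had type I error 4.3–5.0%.

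**Step 5, finite-sample check.** In 3,000 simulated null trials of 69 per arm under the example, type I error was 7.1% for the week-24 difference and 4.9% for the change difference. It was 5.0% with visit-specific variances and 5.3% with baseline as covariate. The Monte Carlo standard error is about 0.4 points.

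**Step 6, when the premise changes.** If the SD falls over follow-up (1.5, 1.4, 1.3), the week-24 ratio is 1.08 and type I error 3.4%: too wide. If eligibility used an earlier sample correlated 0.8 with baseline (mean 8.5, SD 1.5, r = 0.75/0.65), type I error is about 5.6%, against 6.4% when the baseline sample itself was used.

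**Step 7, the alternative.** Selection on baseline does not alter the distribution of week 24 given baseline, so with baseline as covariate the residual SD in the example is 1.5 × √(1 − 0.65²) = 1.140. The change score has variance 1.806 + 1.198 − 2 × 0.779 = 1.446, SD 1.203. The ratio is 0.948, an SE 5% smaller. Over the grid it is 4–13% smaller.

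**The case against.** A reader might infer that the model's week-24 error bars are simply too narrow, or that the trial's main result is at risk. The documents support neither.

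- **Contrast.** The declared outcome is change from baseline. With baseline in the response and time categorical, group-by-time is a natural contrast, and its standard error is about right or slightly conservative. This stands. The article names no contrast for the model, though, so a week-24 difference remains equally open.
- **Wording.** First-order autocorrelation describes correlation; a version with visit-specific variances would also fit the phrase, and the models are to be appropriate and checked by diagnostics. This stands in part. The ordinary fit has one variance, and no replacement is named if the diagnostics fail.
- **Unknown inputs.** The article gives no HbA1c mean, SD or correlation, and step 6 shows that the direction can reverse. This stands and makes the claim conditional. Under either direction, equal variance would be the wrong constraint.
- **Which sample is cut.** Recruitment strategies has eligibility assessed at a consultation, and Allocation concealment lists eligibility and the baseline evaluation as separate items. A separate sample would weaken the effect.
- **Rank.** The model is secondary. The primary analysis uses the week-24 data and does not depend on this covariance. This stands.

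**Conclusion.** The point holds conditionally. The covariance named for the three-visit HbA1c model, as ordinarily fitted, assumes equal variance at all visits, and the trial's own entry rule makes that doubtful at baseline. If the model reports the week-24 arm difference, and truncation is the main source of unequal variance, the SE is likely about 1–10% too small and the type I error about 5–8%. The low end applies when mean HbA1c lies well above 7% relative to its SD. If the model reports the difference in change, there is no anti-conservative error to correct. The primary analysis is untouched. This is a modest and cheap improvement to a secondary analysis, best made before the data are seen because no fallback structure is fixed.

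**What to change.** For the three-visit HbA1c model only, replace the sentence on time and covariance with wording such as: *HbA1c at weeks 12 and 24 will be the outcomes, with baseline HbA1c as covariate, visit as a categorical factor, treatment and treatment-by-visit, and an unstructured within-patient covariance. The reported contrast is the between-arm difference at week 24. A simpler structure will be used only if this model does not converge.*

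This makes the week-24 error bars valid whether variance rises or falls during follow-up.

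The cost is small. An unstructured matrix has 3 parameters for two outcome visits, or 6 instead of 3 if baseline is kept in the response, and 138 patients can support either. No new data are needed.

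Do not carry the unstructured matrix over automatically to the monthly HbA1c series. With about seven time points it would need 7 × 8 / 2 = 28 parameters. Other longitudinal outcomes are not cut by the entry rule, so this argument does not reach them.

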#### Data monitoring

The Data Monitoring Committee (DMC), the Ethics Committee and Trial Steering Committee (TSC) of Second Xiangya Hospital, the latter consisting of endocrinologists, diabetes nurses, nutrition scientists, registered dietitians, certified diabetes educators, and behavioral scientists, will be responsible for monitoring the trial conduct and patient safety and making recommendations for trial modifications or termination based on benefit-risk assessments. The principal investigator (XL) can then decide whether to make changes. The TSC will meet at least once a month to oversee the trial conduct and progress. The frequency of interim analyses will depend on the judgment of the DMC in consultation with the PI.

The DMC, the Ethics Committee, and the TSC are independent of the trial organizer. The chair is [name] Terms of reference for the DMC are available on request from the Clinical Drug Trial Institution at Second Xiangya Hospital.

### Protocol amendments

Any changes to the protocol will involve notification of the trial sponsor first and then the centers, and the clinical trial registry will be updated. A copy of the revised protocol will be added to the Investigator Site File by the PI. Any deviations from the protocol will be fully documented using a breach report form.

### Patient and public involvement

Patients with T1DM were involved in the development of education materials for this study. Patients who meet the inclusion criteria will be recruited and involved in the conduct of the trial. The feasibility of the app will be evaluated by all participants via monthly phone interviews. Study results will be disseminated to the participants on request.

## Discussion

A robust and well-designed RCT will be conducted to determine the effect of an automated, structured education intervention based on an app and artificial intelligence; it has been developed in an evidence-based and culturally tailored manner for the Chinese population for the management of T1DM. The detailed research plan of the RCT is presented in this protocol.

Although evidence had established the effect of smartphone apps in diabetes care, the majority of apps had been developed for T2DM patients and targeted at populations outside of China [10, 11]. According to an updated systematic review [11], only seven trials provided evidence on the effect of smartphone apps among T1DM patients. Pooled results (pooled MD in HbA1c − 0.49%, 95% CI − 0.94 to − 0.04%, *I*^2^ = 83.29%) showed a promising benefit for using smartphone apps to manage T1DM. However, the results from the individual trials were substantially inconsistent (MD of HbA1c varied from − 1.17% [36] to 0.41% [37]), which explained the high level of heterogeneity (*I*^2^ = 83.29%) in the meta-analysis. Furthermore, the results also indicated that the effect of smartphone apps in type 1 diabetes care was still controversial and had a low quality of the evidence [11].

Hence, whether smartphone apps will provide benefits to T1DM patients has not yet been conclusively determined. Very limited effective apps are available for T1DM patients from China. We developed a smartphone app by specifically considering the cultural background and lifestyle of the Chinese population to assist self-management and meet the need for lifelong diabetes care in T1DM patients. In this study, we seek to determine the effectiveness of the newly developed app in type 1 diabetes care compared to routine care.

Moreover, we also plan to explore whether tailoring health education materials by considering the specific knowledge gaps of each individual patient will provide some extra benefits in reducing HbA1c and improving other psychological and psychosocial outcomes. This will facilitate the development of future smartphone apps. As advocated by the latest guidelines, strategies for diabetes management should promote individualized targets and treatments [14]. By including multiple secondary outcomes, this RCT has the chance to explore the potential mechanisms of smartphone apps in improving diabetes care. This will contribute to appropriate outcome selections for future RCTs in diabetes care.

Thus, successful implementation of the proposed RCT will contribute to the evidence base of whether a newly developed smartphone app is superior to routine diabetes care in the Chinese T1DM population. If it is proven to be effective, this study will provide a strategy that satisfies the need for effective lifelong diabetes care to reduce the disease burden and related complications caused by T1DM. The results obtained from this trial are expected to provide important public health implications for T1DM patients in China.

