## Strengths and limitations of this study

➢ The smartphone app evaluated in this trial was developed in a theoretical- and evidence-based manner and contains a digital culturally tailored structured education program specifically targeted at T1DM patients in the Chinese population.

➢ In combination with artificial intelligence technology, automated, individualized education was offered to a group of patients to explore whether tailoring education materials provided to patients might enhance the effects of the smartphone app.

➢ Treatment effects will be measured with a wide spectrum of outcomes, including physiological parameters, psychosocial outcomes, and psychological outcomes, to capture the complex nature of type 1 diabetes.

➢ To avoid potential bias induced by a lack of blinding, we will use an objective outcome (HbA1c) as the primary outcome and will ensure blinding of outcome assessors.

➢ The generalizability of the results generated from this trial will need to be assessed through multicenter trials.

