After considering the needs of both the patients and clinicians, we hypothesized that the implementation of the new SEP strategy would help improve diabetes control for T1DM patients. However, a well-designed RCT is needed to assess the effectiveness of the newly developed app compared to usual care. The present protocol is proposed to serve this purpose. The detailed hypotheses of the RCT are that T1DM patients using the app, as opposed to usual care, will have better diabetes control in terms of HbA1c level, time in range (TIR), quality of life, self-efficacy, and psychological conditions.

This paper presents the details of the design of and protocol for the first RCT assessing the effectiveness of a new SEP based on mobile technology that specifically targeted the T1DM population in China. This study is innovative in that it compares the effectiveness of smartphone apps between usual care and automated, individualized app education to explore whether individualized treatment, as advocated by the latest guidelines [14], will bring any additional benefit to T1DM patients. The ultimate goal is to provide an effective and convenient approach for T1DM control and reduce the related disease burden in China, where the T1DM control status is far from optimal. The protocol of the trial is reported by following the items recommended by the Standard Protocol Items: Recommendations for Interventional Trials (SPIRIT) 2013 statement [15]. The final results will be reported after the RCT in line with the Consolidated Standards of Reporting Trials (CONSORT) 2010 Statement for reporting parallel group randomized trials [16].

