### Intervention

The study interventions will last for 24 weeks. Patients in each of the two groups will be encouraged to continue their previous insulin treatment regimen, with either multiple daily injections or insulin pumps. All the interventions will run concurrently. Patients allocated to the smartphone app group—the automated, individualized education group—will attend a course on the use of the app provided by the research team. The course will be given to the two groups of patients separately to reduce possible contamination.

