The message module facilitates patient-doctor communication through various means: typing words, sending pictures or short videos, sending voice messages, and live chatting. The patient and his/her doctor will establish a blood sugar target collaboratively. The doctor will review the patients’ diabetes diary once a week and provide feedback to patients: (i) give positive feedback if patients are keeping the target well, (ii) alert patients if they are off-target, and (iii) provide other tailored feedback by considering patients’ conditions. Furthermore, whenever a patient’s blood glucose level is dangerous (< 3.9 mmol/L or > 20.0 mmol/L), an alert will be automatically sent to the doctor, and an immediate phone call will be made to the patient by the doctor [13].

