#### Routine care

Patients allocated to the routine care group will receive the education provided by health-care professionals in the outpatient department. They will not be asked to use any smartphone app during the trial. This trial will not require alteration in the use of any medication to both trial arms.

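### The stated aim of exploring whether tailoring adds benefit has no randomised contrast behind it: the two arms compare a whole app package with routine care

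*Protocol article*

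**What the plan says.** **The tailoring aim.** In the Discussion, after stating the aim of comparing the app with routine care, the protocol adds a plan to "explore whether tailoring health education materials by considering the specific knowledge gaps of each individual patient will provide some extra benefits" in HbA1c and in psychological and psychosocial outcomes. It expects the answer to help in developing later apps. The Strengths and limitations list says individualised education is offered "to explore whether tailoring education materials provided to patients might enhance the effects of the smartphone app". The Background calls the study innovative because "it compares the effectiveness of smartphone apps between usual care and automated, individualized app education to explore whether individualized treatment" brings an additional benefit.

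**The design.** The Overview of the study design says: "Patients with T1DM will be randomly allocated into one of two groups". Sample size estimation gives 69 patients to each. The Data analysis section plans one between-group contrast, app group versus routine care group. For controls, the Routine care section says: "They will not be asked to use any smartphone app during the trial".

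**What the app arm receives.** The structured education material has a tailored part with push notifications and a second part that patients browse freely without them. The same patients also have:
- glucose and lifestyle diaries, general diabetes information and access to their records;
- messaging with a doctor, who reviews the diary "once a week and provide feedback to patients";
- automatic glucose alerts that prompt a doctor's phone call;
- adherence reminders, and small gifts for the most frequent users.

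**The course.** The Intervention section first says that patients allocated to the app group attend a course on using the app. It then says: "The course will be given to the two groups of patients separately to reduce possible contamination".

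**The concern.** Words such as extra benefit, and enhancing the effect of the app, pose a second question: does a tailored app do better than the same app without tailoring? Answering it needs patients who have the app without the tailoring, and the design has none.

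What is at stake is how a positive result is read. If the tailoring aim stays in the protocol, a difference between the arms could be reported as evidence that automated individualisation works, although the arms also differ in clinician contact and several other features. Since the protocol wants the finding to guide later apps, a reader could keep the tailoring and drop a component that did the work.

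The course sentence is a smaller matter. It speaks of two groups receiving app instruction when only one group has the app.

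**Working it through.** **1. The plan's own numbers.** Inputs from Sample size estimation: 110 evaluable patients, 20% drop-out, difference 0.6% HbA1c, two-sided 5% level, 80% power, 1:1 allocation.
- Inflation: 110 / (1 − 0.20) = 137.5, rounded up to 138, or 69 per arm. This reproduces.
- No SD is given. With n per arm = 2 × (1.960 + 0.842)² × SD² / 0.6² set to 55, SD = 0.6 × √(55/2) / 2.802 ≈ 1.12.

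All 138 patients are thus sized for the package-versus-routine-care difference.

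**2. Can tailoring be separated?** Treat tailored push material and everything else in the app package as two factors.

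| Tailoring | Rest of package | Patients randomised |
|---|---|---|
| yes | yes | 69 (app arm) |
| no | no | 69 (routine care) |
| no | yes | 0 |
| yes | no | 0 |

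Let T be the effect of tailoring alone, O that of the rest of the package alone, and I their interaction. The trial estimates one quantity:

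app − routine care = T + O + I

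One equation cannot give three unknowns. With I = 0 and an observed reduction of 0.6%, T = 0.6 with O = 0, T = 0 with O = 0.6, and every split between them fit the data equally well. More patients make the sum more precise but do not divide it.

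**3. Does anything else in the plan vary tailoring?**
- The app-engagement measures (education messages sent, time in the education module and so on) vary within the app arm, but not by randomisation. No analysis of tailoring is tied to them.
- The moderators given as examples are depression, anxiety and self-efficacy. They address who responds, not which component works.
- No factorial element or second randomisation is described.

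**4. How much else differs?** Weekly review over 24 weeks is 1 × 24 = 24 planned doctor reviews per app patient. The frequency of contact under routine care is not stated, so the net difference is unknown.

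**5. What answering the question would take (illustration only).** Suppose an untailored-app arm were added. Assume SD 1.11, the value at which a t-test with 55 per arm has about 80% power for 0.6%, and a tailoring increment of 0.3%. Neither figure is in the protocol.
- n per arm = 2 × 2.802² × 1.11² / 0.3² ≈ 215 evaluable.
- 215 / 0.8 = 268.75, so 269 randomised per arm and 3 × 269 = 807 in three arms.
- Over SD 1.0 to 1.5 the need is 175 to 393 evaluable per arm.
- With 55 evaluable per arm, power would be about 29% (35% at SD 1.0, 18% at SD 1.5).

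**6. The course sentence.** The sentence before it assigns the course to the app group, the app section gives installation instructions to that group only, and controls are not asked to use an app. The two-groups sentence conflicts with all three.

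**The case against.** The strongest case on the other side has four parts.

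**The aim is only exploratory.** The protocol never says it will test tailoring. The verb is explore in all three places, and the hypotheses, sample size and planned contrast are all app versus usual care. This is correct, and it limits the point: no confirmatory claim fails. It does not rescue the aim, because an exploratory question also needs a contrast in which tailoring varies.

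**The Background sentence can be read differently.** It names usual care as the comparator, so its closing clause, "to explore whether individualized treatment, as advocated by the latest guidelines [14], will bring any additional benefit to T1DM patients", may mean benefit over usual care, which the trial does estimate. This stands. The Background is ambiguous support; the Discussion and the Strengths list are the clear cases.

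**The intended conclusion is already about the whole app.** The Discussion closes on whether the app is superior to routine care, and the components are openly described. Comparing a package with usual care is a legitimate design. This also stands, and it shows that the tailoring sentences can be removed without loss.

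**The contact imbalance is easily overstated.** The four-weekly adverse-event calls are not limited to one arm, and the Patient and public involvement section gives monthly phone interviews to all participants. Only the weekly review, alerts, app messaging, app reminders and gifts are specific to the app arm.

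A reader might also infer from the course sentence that controls will be taught the app and the effect biased toward zero. The surrounding text limits both the course and the app to the app group, so the documents do not support that. Nor do they support the inference that the wording survives from a design with two app groups: no such design is described, and the Trial status section calls this version 1.

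**Conclusion.** The point holds as a mismatch between a stated exploratory aim and the design. The Discussion and the Strengths list, and less clearly the Background, promise information on what tailoring adds. The only randomised contrast is the whole package against routine care, and zero patients are allocated to an untailored app, so no tailoring or other component effect can be identified. This follows from the two-arm structure and rests on no assumed SD or effect size.

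The consequence is confined to that aim and to conclusions drawn from it. The primary HbA1c comparison, its power and its error rate are untouched. A reader might go further and say that a positive result could equally be due to weekly clinician contact. The documents give no basis for apportioning the effect in either direction; they show only that it cannot be apportioned.

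The course sentence is a drafting inconsistency to reconcile, not demonstrated contamination.

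**What to change.** - In the Discussion and the Strengths and limitations list, delete the tailoring aim, or restate it as the effect of the whole app package, including clinician feedback and alert calls, versus routine care.
- In the Background, make clear that the additional benefit meant is benefit over usual care.
- State once that no effect of an individual component will be inferred.
- Report the engagement and contact counts already being collected as a description of what was delivered, not as evidence for tailoring.
- In the Intervention section, reconcile the two-groups sentence with the sentence before it and with the Routine care section, so that the course is described for the app group only.

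The cost is a few sentences and a narrower claim. Arms, numbers and data collection do not change. If the sponsor wants the tailoring question answered, that needs a randomised untailored-app comparator with its own sample size, which on the illustrative assumptions above is several times the present trial.
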